### Outcomes

Primary, secondary and additional outcome measures, including the specific measurement variables, timeframe and instruments, are shown in table 2.

**Table 2 T2:** Primary, secondary and additional outcome measures, including the specific measurement variables, timeframe and instruments

Outcome measures	Instruments
Primary outcome measuresTimeframe: baseline (week 0) and after 12-week intervention (weeks 13 and 14)Analysis metric: change from baseline	
PA level and pattern of PA in the type of PA (work, active commuting, exercise, etc.), type of exercise, duration of each session (time spent in PA), weekly frequency and intensity and weekly volume (MET-min/week).	PPAQ^21^ and get active questionnaire for pregnancy^22^
Self-perceived fitness: self-perceived global fitness and fitness components (cardiorespiratory, strength, speed/agility and flexibility) when compared with other women of the same age. Likert scale 1 (poor) to 5 (very good).	IFIS^23^
Cardiorespiratory fitness estimated in mL/kg/min	Cardiorespiratory fitness—6-min walk test (average distance covered in metres and estimated cardiorespiratory fitness in mL/kg/min)^24^https://youtu.be/CUaFgfdSObc
Upper limbs strength	Upper limb strength—wall push-ups (number of repetitions in 30 s)^6 17^https://youtu.be/dp_tRoyxVYU
Lower limbs strength	Lower limb strength—sit-and-stand (number of repetitions in 30 s)^6 17 25^https://youtu.be/3ihcqnzyTXk
Dynamic balance	Dynamic balance—superwoman^6 17^https://youtu.be/Xiv_vWpe4-A
Static balance	Static balance—one-leg stance^6 17^https://youtu.be/sr0eYCfbLiM
Lower limbs flexibility	Lower limbs flexibility—modified sit and reach (mm)^6 17^https://youtu.be/Y6y_FAa3ulk
Upper limbs flexibility	Upper limbs flexibility—back scratch (mm)^6 17^https://youtu.be/MBwKi8kSFx8
Agility	Agility—time up and go over 3-m distance (in min)^6 17^https://youtu.be/3C944cMuTFo
Secondary outcome measuresTimeframe: baseline (week 0) and after 12-week intervention (weeks 13 and 14)Analysis metric: change from baseline	
Sleep quality	PSQI^26^
Weight prepregnancy, weight at baseline and weight gain (kg)	Body weight: measure with the participant wearing light clothing and without shoes^27^
Happiness scale	SHS^28^
Depression scale	EPDS^29^
Adherence to the Mediterranean diet	MEDAS^30^
HR	Measured rest HR, estimated maximal HR and calculated target HR (beats per minute)

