### Statistical methods for primary and secondary outcomes

Demographic data (age, weight, gestational age, area of residence and date of birth) will be described using frequencies and percentages for categorical variables.

Descriptive statistics (mean, SD, median and IQR) will be used to summarise baseline characteristics of participants in both groups (IN and ON).

Descriptive and inferential statistics will be applied to all outcomes.

A comparative analysis of IN *versus* ON interventions will be conducted using both intention-to-treat and per-protocol approaches. Comparative analysis will be used to compare changes in primary and secondary outcomes between IN and ON groups over time (baseline and postintervention). Subgroup analyses will evaluate potential differences between maternal age groups (<35 *vs* 35+ years) and PA level groups.

Adherence to the intervention (proportion of attendance in the planned sessions) will be calculated after the postintervention assessments.

Data from participants who do not complete at least 80% of the scheduled sessions will be considered a loss to follow-up.

Regarding additional outcome analysis, the evaluation of interventions and resources will be performed through descriptive analysis, summarising satisfaction with resources and exercise interventions.

Continuous variables will be assessed for normality using Shapiro–Wilk tests. Normally distributed variables will be presented as mean±SD and analysed using the independent sample t-test. The non-normally distributed data will be reported as the median with IQR and will be analysed using the Mann–Whitney test. For the within-group difference, normally distributed variables will be calculated with the paired-sample t-test. In contrast, those non-normally distributed variables will be calculated with the paired-sample non-parametric Wilcoxon test. Categorical data will be analysed using Pearson’s χ^2^ test or Fisher’s exact test, as appropriate.

A significance level of 0.05 (alpha level) will be set for all statistical tests. Power calculations were performed to ensure that the study was adequately powered to detect clinically significant differences between groups. All statistical analyses will be conducted in Statistical Package for the Social Sciences.

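### The analysis rules do not provide for the ordinal primary fitness ratings: one route reports a coarse median of integer changes, the other ignores the order of the levels, and neither gives an effect estimate with an interval

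*Protocol article*

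**What the plan says.** Table 2 (Outcomes) lists self-perceived fitness, measured by IFIS, as one of ten rows of primary outcome measures. The row covers global fitness and four components, rated on a "Likert scale 1 (poor) to 5 (very good") scale. The metric for all primary outcomes is "Analysis metric: change from baseline". The table does not describe a summed score.

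The section on statistical methods for primary and secondary outcomes has two classes of variable.

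- Continuous: "Continuous variables will be assessed for normality using Shapiro–Wilk tests". If the test passes, "Normally distributed variables will be presented as mean±SD and analysed using the independent sample t-test". If it fails, "The non-normally distributed data will be reported as the median with IQR and will be analysed using the Mann–Whitney test".
- Categorical: "Categorical data will be analysed using Pearson’s χ^2^ test or Fisher’s exact test, as appropriate".

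There is no rule for ordered categories, and nothing assigns the IFIS ratings to either class. The Trial design section declares an equivalence framework.

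**The concern.** The change in a single five-level rating is an integer from −4 to +4. Its median can move only in steps of a whole category, or half a category when the sample size is even. It can therefore stay the same while the arms differ, or jump while they do not. An unordered test treats a one-level gain and a one-level loss as just two different labels.

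Equivalence is judged from an effect estimate and its interval. For these ratings the stated rules give a pair of medians with a p-value, or a p-value alone. A published median change of 0 in both arms could be taken as evidence that in-person and online delivery are equally effective, which is what the trial hypothesises. The baseline rating enters only through subtraction and is never used as a covariate.

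**Working it through.** **Inputs from the article.** Five levels, change from baseline, and the Shapiro–Wilk rule with its routes. "A significance level of 0.05 (alpha level) will be set for all statistical tests". The plan is 100 per group with 20% expected loss, so 100 × (1 − 0.20) = 80 evaluable per group.

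**The plan's own figure.** The article gives no planning figure for the IFIS ratings. Its two-group size of 59 per group cannot be reproduced, because the means and SDs behind it are not given. With 80% power and two-sided 0.05 it implies a standardised difference of (1.960 + 0.842) × √(2/59) = 0.516. With 80 per group the same formula gives 2.802 × √(2/80) = 0.443. A difference of about 0.4 SD is thus of the order the trial could hope to detect.

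**Model (assumptions).** Latent baseline b ~ N(0,1). Latent follow-up p = ρb + √(1 − ρ²)e + s + d·arm, with e ~ N(0,1), ρ = 0.5 or 0.7, s a shift shared by both arms and d the true difference. Both are cut into five levels with baseline shares 5/20/40/25/10% or 10/30/40/15/5%. Change is follow-up level minus baseline level, and chi-square is applied to the change categories.

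**Step 1: which route?** Shapiro–Wilk rejected in 100% of simulated trials. If the ratings count as continuous, the mean and t-test route is closed in practice.

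**Step 2: the median summary, 80 per arm, d = 0.4 SD (about 0.4 point).**

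| Shared shift s | Trials with identical medians |
|---|---|
| none | about 76–85% |
| +0.2 SD | about 23–29% |

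A separate simulation used shares 5/20/45/25/5%, 80 or 100 per arm and 400 trials per scenario (error up to about ±5 points):

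| Shared shift s | d = 0.25 SD | d = 0.4 SD | d = 0.5 SD |
|---|---|---|---|
| none | 98–100% | 88–94% | 68–75% |
| +0.3 SD | 56–64% | 11–21% | 3–8% |
| +0.6 SD | 48–50% | 46–57% | 44–54% |

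With s = +0.6 SD and no true difference, the medians agreed in only 40–47% of trials. They therefore differed, by half a category or a whole one, in 53–60%. The result turns on where the change distribution sits relative to a step.

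**Step 3: the tests, 80 per arm, d = 0.4 SD, no shared shift.**

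| Analysis | Power |
|---|---|
| Chi-square on change categories | about 32–58% |
| Mann–Whitney on change | about 60–80% |
| Linear regression, baseline as covariate | 76–87% |
| Proportional odds, baseline as covariate (250 trials per scenario) | 73–92% |

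Among the no-shift trials whose medians tied, Mann–Whitney was still significant in 52–77%. In the separate simulation it was within about 3.5 points of a t-test on mean change, and mean change recovered the true difference in every scenario (for example about 0.34 point at 0.4 SD).

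**The case against.** The strongest reply is that the sentence prescribing the median also prescribes Mann–Whitney. That test uses the full ordering and loses almost nothing against a t-test. This stands: on the continuous route the planned test is sound.

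A reader might infer that the two arms will usually show the same median, or that the result will support equal effectiveness whatever the truth. The article supports neither. It hypothesises a benefit in both environments, and a shared gain of 0.2 SD already cuts the share of tied medians to about 23–29%. A tie would often be printed beside a significant Mann–Whitney p-value, which is no support for equality.

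A reader might also credit ordinal modelling with the higher power. Linear regression with baseline reaches 76–87%, so most of the gain comes from baseline adjustment, which would help other primary outcomes too.

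It is also fair that the article never assigns the ratings to the categorical class, so the power loss with chi-square is conditional on that reading. The absence of an interval is not peculiar to IFIS either.

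Finally, an article may leave detail to the full protocol, which it says is available on request. That would answer mere silence. Here the article states rules for its primary and secondary outcomes, and those rules fit this outcome poorly on either reading.

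**Conclusion.** The point holds in a limited form. The article does not say how the ordered IFIS ratings are classed. Read as continuous, they get a summary that can hide a real difference or suggest one that is small or absent; the test is valid, but there is no effect estimate with CI and the baseline score is not used as a covariate. Read as categorical, they get a test that ignores order, with power of about 32–58% instead of 60–80% in the no-shift scenarios.

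This rests on the ratings being analysed singly, on the reported median being that of the change (the metric in Table 2), and on assumed distributions, correlations and shifts. It concerns one of ten primary rows. It should be corrected, but it does not invalidate the trial.

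**What to change.** For the IFIS ratings, state that each is analysed singly (or define the combined score). Replace the Shapiro–Wilk rule with a regression of the weeks 13–14 score on arm, with the baseline score as covariate. Name one model in advance: proportional odds, reporting the common odds ratio with its CI, or linear, reporting the adjusted mean difference in points with its CI. Show the full distribution of scores by arm and visit. Do not rely on medians of change or on an unordered chi-square.

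The cost is analysis wording. The baseline score is already collected, no visit or participant is added, and ordinal regression is available in the package the article names. The small downside is a model assumption, which the distribution table lets readers check.

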Prevalence of pregnancy-related symptoms and health parameters (eg, weight gain, blood pressure, prevalence of gestational diabetes or hypertension and contraindications for PA)	Medical records, pregnancy symptoms inventory and get active questionnaire for pregnancy^22^
Other prespecified outcome measuresTimeframe: after the intervention (13 and 14 weeks)	
Participant satisfaction with the available resources—Likert scale (1–5, with 1 not satisfied at all, and 5 highly satisfied).	Satisfaction with educational digital resources (ie, ACTIVE PREGNANCY Guide, YouTube channel ACTIVE PREGNANCY and the framework of the ACTIVE PREGNANCY app).
Participant satisfaction with the intervention—Likert scale (1–5, with 1 not satisfied at all, and 5 highly satisfied).	A questionnaire explicitly made for the intervention evaluating different domains: type of exercises, hardness of the sessions, difficulty in particular exercises, weekly frequency, duration of the sessions, context of intervention (online, outdoor, gym and hospital), satisfaction with the exercise physiologist, willingness to continue in postpartum, willingness to repeat in future pregnancy and overall satisfaction to be included in the programme.
Feasibility and adherence	Feasibility evaluation of the implementation of the exercise programme: (1) number of women who declined to participate in the study; (2) number of women who gave up participation in the study; (3) adherence to the programme (number of days of actual performance of the exercise programme while admitted) and (4) number of women who completed at least 80% of the study.

EPDS, Edinburgh postpartum depression scale; HR, heart rate; IFIS, International Fitness Scale; MEDAS, Mediterranean Diet Adherence Screener; MET, metabolic equivalent; PA, physical activity; PPAQ, pregnancy physical activity questionnaire; PSQI, Pittsburgh sleep quality index; SHS, subjective happiness scale.

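### The only tests named for categorical data are unpaired, so within-arm change in the secondary prevalence outcomes has no test of no change

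*Protocol article*

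**What the plan says.** The section on statistical methods for primary and secondary outcomes assigns tests by type of variable. For continuous variables it separates two uses. Between groups, it names the independent-sample t-test or Mann–Whitney. Within groups, it states: "For the within-group difference, normally distributed variables will be calculated with the paired-sample t-test", and "those non-normally distributed variables will be calculated with the paired-sample non-parametric Wilcoxon test". One sentence then covers every categorical variable: "Categorical data will be analysed using Pearson’s χ^2^ test or Fisher’s exact test, as appropriate". No paired categorical test is named anywhere in the article.

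The same section promises that "Descriptive and inferential statistics will be applied to all outcomes", and describes the comparative analysis as one that will "compare changes in primary and secondary outcomes between IN and ON groups over time (baseline and postintervention").

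In Table 2 (Outcomes), the secondary block has two time points, baseline and after the 12-week intervention, and carries the line "Analysis metric: change from baseline". One row of that block is "Prevalence of pregnancy-related symptoms and health parameters", with gestational diabetes, hypertension and contraindications to physical activity among its examples.

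**The concern.** A symptom recorded as present or absent at both visits gives paired binary data. The question of change within an arm is whether the two marginal prevalences are equal. Pearson's and Fisher's tests address a different null, that of independence between rows and columns, and they assume that each count comes from a different woman.

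If the sentence on categorical data is followed literally for within-arm change, an analyst has two ways to apply it:

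- **Stacked table (time by outcome).** Baseline and post counts are treated as two independent samples. The variance leaves out the within-woman covariance, so with positive correlation it is too large and real changes can be missed.
- **Cross-table (baseline status by post status).** The test asks whether post status is related to baseline status. It rejects when symptoms persist, whether or not prevalence has changed.

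At stake are the within-arm p-values for the health parameters, which are a secondary objective.

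**Working it through.** **Inputs from the article.** 100 women per arm and 20% expected loss (Sample size), so 100 × (1 − 0.20) = 80 per arm; alpha 0.05 (Statistical methods), taken as two-sided. The stated sample sizes of 36 and 59 per group rest on means and SDs, not on a categorical outcome, so the plan has no figure of its own to reproduce here.

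**Assumptions, not in the article.** Prevalence 40% at baseline; 40% (no change) or 55% afterwards; within-woman correlation phi from 0 to 0.6.

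**Step 1: variance of the change in prevalence.**
- Stacked: [p1(1−p1) + p2(1−p2)]/n = (0.2400 + 0.2475)/80 = 0.00609, SE 0.078, so 0.15/0.078 = 1.92.
- Paired: subtract 2·phi·√[p1(1−p1)p2(1−p2)]/n, where the root is √(0.2400 × 0.2475) = 0.2437.
  - phi 0.3: (0.4875 − 0.1462)/80 = 0.00427, SE 0.065, ratio 2.30.
  - phi 0.5: (0.4875 − 0.2437)/80 = 0.00305, SE 0.055, ratio 2.72.

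**Step 2: size of the stacked test with no change.** With equal prevalences the true variance is (1 − phi) times the one assumed, so the effective critical value is 1.96/√(1 − phi).
- phi 0.3: 2.34, size about 1.9%.
- phi 0.5: 2.77, size about 0.6%.

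The test is conservative; it does not produce excess false positives.

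**Step 3: simulation, n = 80, 400,000 runs per row.** Power for 40% to 55%:

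| phi | stacked chi-square | exact McNemar | mid-p McNemar |
|---|---|---|---|
| 0 | 47% | 41% | 47% |
| 0.1 | 47% | 45% | 51% |
| 0.2 | 47% | 49% | 55% |
| 0.3 | 46% | 54% | 60% |
| 0.5 | 45% | 70% | 76% |
| 0.6 | 45% | 81% | 87% |

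With no change, the stacked test rejects in 1.8%, 0.5% and 0.2% of runs at phi 0.3, 0.5 and 0.6; mid-p McNemar stays between 4.4% and 4.8% over the whole range of phi. A separate set of runs at 30% to 45% gives the same pattern: stacked 50% and 49%, against exact McNemar 57% and 73%, at phi 0.3 and 0.5.

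**Step 4: the cross-table.** Its chi-square has noncentrality of about n·phi². At phi 0.3 this is 80 × 0.09 = 7.2, so with no change in prevalence it rejects about 77% of the time (simulated 77%). At phi 0.5 and 0.6 it rejects in essentially every run.

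**Step 5: the comparison between arms.** With two independent arms of 80 or 100 and a true prevalence of 10% or 30%, Pearson's test rejects in 4.9% to 5.2% of runs. It is valid there.

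**Step 6: conditions absent at baseline.** For 0/80 before and x/80 after, Fisher gives p = 0.059 at x = 5 and 0.028 at x = 6. Exact McNemar gives 2 × 0.5^5 = 0.063 and 2 × 0.5^6 = 0.031. Both first reach significance at six cases, so nothing is lost in practice.

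**The case against.** A reader might infer that the plan expressly assigns Pearson or Fisher to before-after comparisons. It does not. The sentence is general, the phrase on within-group difference introduces only the continuous tests, and the stated comparative analysis is between randomised arms, where these tests are correct. That stands. Even so, the sentence is not limited to that use. It directly follows the within-group tests, and the qualifier at its end most naturally chooses between two tests that are both unpaired.

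A reader might also infer that the high rejection rates of the cross-table are a false-positive rate of the planned analysis. Nothing in the article proposes that table; the figures show only what it would test.

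Nor do the documents support a general claim of large power loss. They give no within-woman correlation. At phi 0.2 the stacked test is about 2 points below exact McNemar and 8 below mid-p; at 0.1 or less it does better than the exact test.

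The scope is narrow too. The affected row also contains continuous items. Eligibility requires healthy women and excludes conditions that contraindicate activity, so contraindications are near zero at baseline, and gestational diabetes and hypertension are likely to be mostly new-onset. The self-rated fitness scale is a primary outcome on a five-point scale, but the article does not class it as categorical, and the Wilcoxon and Mann–Whitney tests already named can handle it.

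Finally, a separate analysis plan may name a paired test. Silence alone would therefore be no finding. The point survives because the article states a rule for all categorical data that, read literally, puts unpaired tests on paired outcomes. It is also fair that, with no untreated arm, even a correct within-arm test cannot separate the programme's effect from advancing gestation.

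**Conclusion.** The point holds as a minor one. The article names paired tests for continuous within-group change and only unpaired tests for categorical data, although the secondary prevalences are measured twice in the same women and defined as change from baseline. For moderate correlation the cost of the stacked form is about 8 points of power against exact McNemar at phi 0.3 and 25 points at phi 0.5 (14 and 31 against mid-p). These sizes rest on the assumed 40% to 55% and 80 women per arm. Symptom prevalence is the one outcome likely to resemble that setting. The primary outcomes and the validity of Pearson or Fisher for IN versus ON are not in question.

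**What to change.** Amend the sentence on categorical data in the statistical methods section:

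- Limit Pearson's and Fisher's tests to comparisons between independent women.
- For within-arm change in a binary outcome, use McNemar's test (mid-p or exact; choose one in advance) with a paired 95% confidence interval for the change in prevalence. For more than two categories, use the marginal-homogeneity test.
- For IN versus ON, compare post status adjusted for baseline status and for site, the randomisation stratum, for example by logistic regression reported as a risk difference. Where baseline prevalence is about zero, compare new-onset cases among women free of the condition at baseline.

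The cost is a few sentences, written before the data are analysed. No new data are needed. McNemar and marginal-homogeneity tests are available in the package already named, and the mid-p value follows from the two discordant counts.

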## Abstract

Many studies have supported the positive effects of an active lifestyle on the prevention and treatment of pregnancy-related complications, as well as maintaining fitness and functionality. The COVID-19 pandemic has underscored the need for virtual approaches to health interventions; however, few studies have examined the effectiveness of these interventions. The Standard Protocol Items: Recommendations for Interventional Trials 2025 guidelines were followed to describe the protocol of the ACTIVE PREGNANCY trial, an intervention study that delivers a physical exercise programme in-person (IN) and online (ON) to improve maternal physical activity (PA), fitness and healthy lifestyle parameters in pregnant women. Pregnant women will be invited to participate in a multisite, multicomponent exercise programme delivered either IN or ON by qualified exercise physiologists. Both groups will receive an exercise intervention delivered in different real-life environments. Participants will undergo basic fitness field tests and complete questionnaires assessing PA, fitness and lifestyle parameters before starting the exercise programme and after completing 12 weeks of the intervention. Researchers will test whether the intervention is beneficial in maintaining or improving maternal parameters after 12 weeks and will compare the effectiveness of different exercise modes. Subgroups of maternal age and weekly volume of PA will also be analysed.

Primary outcomes: PA volume and health-related and functional fitness. Secondary outcomes: healthy lifestyle parameters. Additional outcomes: satisfaction with the exercise interventions and resources. This study was approved by the Ethics Committee of Santarém Polytechnic University and registered on ClinicalTrials.gov (NCT06954454). Findings will be disseminated via publications, conferences and training programmes.

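### Ten unranked primary outcomes are each tested at an unadjusted 0.05, so the error rate across the primary outcomes is not controlled

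*Protocol article*

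**What the plan says.** The block of Table 2 (Outcomes) headed "Primary outcome measuresTimeframe: baseline (week 0) and after 12-week intervention (weeks 13 and 14)Analysis metric: change from baseline" has ten rows: physical activity (PA), self-perceived fitness, cardiorespiratory fitness, upper limb strength, lower limb strength, dynamic balance, static balance, lower limb flexibility, upper limb flexibility and agility.

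Three rows hold more than one variable:
- The PA row includes "type of exercise, duration of each session (time spent in PA), weekly frequency and intensity and weekly volume (MET-min/week".
- The self-perceived fitness row covers "self-perceived global fitness and fitness components (cardiorespiratory, strength, speed/agility and flexibility", which is five ratings.
- The walk test yields "average distance covered in metres and estimated cardiorespiratory fitness in mL/kg/min".

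The abstract is shorter: "Primary outcomes: PA volume and health-related and functional fitness". The Objectives section spreads the primary comparison over PA, self-perceived fitness and fitness, and puts none of them first.

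The statistical methods section says "Descriptive and inferential statistics will be applied to all outcomes" and, on the error rate, "A significance level of 0.05 (alpha level) will be set for all statistical tests". Trial design calls the trial an equivalence trial.

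**The concern.** With ten primary outcomes of equal standing and 0.05 for each test, the 5% describes each test alone. It does not describe the trial's main conclusion, because nothing in the article links ten results to one conclusion. One significant row could be reported as a difference between delivery modes, and one favourable row could be reported as equivalence. In either case the chance of error is well above the nominal level. If the deciding row were picked after the results were known, the conclusion would have no defined error rate.

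This is more than a detail left to an unseen analysis plan. The article itself fixes both the ten primary rows and the 0.05 for every test.

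**Working it through.** **Inputs**
- From Table 2: k = 10 primary rows, counted as one test each.
- From the statistical methods: alpha = 0.05 per test. Sidedness is not stated, so two-sided is assumed for differences.
- Assumed: a common correlation r between the test statistics of 0, 0.3, 0.5 or 0.7. The article gives none.
- Scope: between-group tests in one analysis set.

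The article gives no family-wise figure to reproduce.

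**1. At least one false difference, when no row truly differs**

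Independent rows: 1 − (1 − 0.05)^10 = 1 − 0.95^10 = 1 − 0.599 = 0.401.

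Correlated rows: with equicorrelated normal statistics, the chance that any |Z| exceeds 1.96 was found by simulation (400,000 draws) and by numerical integration. The two agree.

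**2. At least one false equivalence claim, in the worst case**

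Suppose every row truly lies at its margin, on the same side, and is tested at 5% one-sided. Independent rows again give 1 − 0.95^10 = 0.401. For correlated rows, the chance that any Z exceeds 1.645 was found by numerical integration.

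| Assumed correlation | False difference on at least one row | False equivalence on at least one row |
|---|---|---|
| 0 | 40% | 40% |
| 0.3 | 35% | 31% |
| 0.5 | 29% | 25% |
| 0.7 | 21% | 19% |

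**3. If all ten rows had to succeed**

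A false overall claim then requires every row to pass, so 0.05 per row is enough without adjustment. The cost is power, which depends on a margin that the article does not give. As an illustration, take two one-sided tests at 5%, a true difference of zero, independent rows and 80 evaluable per arm (100 planned less 20% loss). The standard error in SD units is √(2/80) = 0.158. Power per row is 2Φ(margin/0.158 − 1.645) − 1.

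| Assumed margin | Power per row | All ten rows |
|---|---|---|
| 0.4 SD | 62% | 0.62^10 ≈ 1% |
| 0.5 SD | 87% | 0.87^10 ≈ 25% |
| 0.6 SD | 97% | ≈ 73% (unrounded 0.968^10) |

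**4. What adjustment over ten rows would cost**

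The Sample size section gives 59 per group for power 0.8 at 0.05, without the outcome or its SD. Solving a two-sided two-sample t-test backwards gives a standardised difference of 0.52. With 80 evaluable per arm, power at that difference is 90.5% at 0.05. At 0.05/10 = 0.005, the first Holm step, it is 67.1%. These are powers for detecting a difference, not for showing equivalence.

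**The case against.** The strongest reply is that a success rule may stand in the full protocol or analysis plan. The Data management section says the full protocol can be requested, and the hypothesis in the Introduction is that both environments are equally effective. If that meant equivalence on every row, 0.05 per test would be valid. This limits the point but does not remove it: the article does not state such a rule, and its text sets 0.05 for all tests on ten primary rows.

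Four stronger readings are tempting, and the document does not support them.
- **That success on all ten rows is improbable.** A reader might assume 80% equivalence power per row and get 0.8^10 ≈ 11%. But the 0.8 in the Sample size section is power for detecting differences. Without a margin, the all-ten figure runs from about 1% to 73% over the margins shown above.
- **That the age and PA subgroups inflate the primary error further.** The Objectives section makes subgroup differences a secondary aim, outside the primary family.
- **That every component counts as a further primary test.** Splitting the rows into about 16 variables (an assumed count) would give 1 − 0.95^16 = 56% if independent. But the abstract narrows PA to its volume, and the two walk-test metrics come from one test. Ten is the safer count.
- **That 6-minute walk distance should be the deciding outcome.** The abstract and objectives list PA first. The Data collection methods section allows field tests in person or online, and the outcome assessors are unblinded, so a performance test is not clearly safer than a self-report.

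**Conclusion.** The point holds in this form: ten unranked primary rows, each tested at an unadjusted 0.05, with no stated rule for combining them. If any significant row counts as a difference, the chance of at least one false difference is 40% under independence and 21% at a correlation of 0.7, at least four times the nominal 5%. Worst-case false equivalence on at least one row runs from 40% to 19% over the same range. The correlations are assumptions. The equivalence figures also assume that every row lies at its margin and is tested at 5% one-sided. No conclusion is drawn about the power of an all-ten rule, because the margin is not given. The point deserves correction during the trial and is cheap to correct.

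**What to change.** Replace the blanket 0.05 with a rule that controls error across the primary outcomes. Either of these would do:
- Name one deciding primary variable, chosen by the authors and measured comparably in both arms. Move the others to secondary, reported with confidence intervals.
- Keep the ten rows, fix one variable for each, and state a Holm adjustment, a fixed hierarchy or an explicit all-must-succeed rule.

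The article reports recruitment from May 2025 and interim analyses by the steering group every 3 months. The choice should therefore be made by people without access to interim comparative results, dated, and entered in the registry.

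The cost is a wording change in the protocol and the registry, with no data lost. With a single primary variable, unadjusted claims on the other outcomes are given up. With Holm, power per outcome is lower: at the back-solved difference of 0.52 it falls from 90.5% to 67.1% at the strictest step. With an all-must-succeed rule, power has to be worked out once a margin is set.
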